### Plans to give access to the full protocol, participant level-data and statistical code {31c}

The full protocol and statistical code will be publicly available. A deidentified anonymous dataset will also be publicly available.

## Oversight and monitoring

### Composition of the coordinating centre and trial steering committee {5d}

The trial management and oversight are governed by three trial committees and groups: the Trial Team (TT), the Trial Management Group (TMG), the Joint Trial Steering and Data Monitoring Committee (SDMC). The TT is responsible for running the trial operations on a day-to-day basis, maintaining trial databases, randomising clusters, ensuring complete and correct data, and preparing reports for meetings (including those of the TMG, and the SDMC). The TT will also address research governance and regulatory matters wherever needed. The TMG will be responsible for managing the trial, including its clinical and practical aspects as well as technical aspects and any safety issues related to the trial participants. In addition, the TMG will also be responsible for providing inputs to the SDMC meetings.

### Composition of the data monitoring committee, its role and reporting structure {21a}

In this trial an SDMC will be used. The SDMC’s responsibility is to oversee and safeguard the trial and the trial participants, monitor the main outcome measures including safety and efficacy, and monitor the overall progress of the trial. The SDMC also receives and reviews information on the accruing data of this trial and provides advice on the trial to the TMG. The relationship between the groups is briefly described in Fig. 4. Details of the composition, roles, and meeting frequency of the TT, TMG, and SDMC are tabulated in the Table 3.

**Fig. 4 Fig4:**
[figure not shown]
Trial organisation overview

## Adverse event reporting and harms {22}

In line with other current trials that include critically ill patients [52], we will not collect adverse events or serious adverse events, because many of these events are expected in this patient population. In addition, we already collect many of these events, such as mortality, as part of our outcomes. We will only report safety events if they are life-threatening, prolong hospitalisation or result in meaningful harm to the participant. It is difficult to predefine a comprehensive list of events that can be considered safety events, but we will actively assess the presence of the following safety events:Prolonged mechanical ventilation (> 7 days)Initiation of renal replacement therapyProlonged (> 2 days) or renewed (restarting after at least 2 days) use of vasopressors such as norepinephrine or vasopressin

These are considered safety events because they may suggest pulmonary, renal, septic or bleeding complications, and an increase in their occurrence following ATLS® training may indicate that the intervention is harmful. These events must therefore be tracked during the standard care phase as well as the intervention phase. However, these events will be considered indicative of harm related to the intervention only if they occur more often during the intervention phase than during the standard care phase. In addition, safety reports other than those mentioned above will be collected. These events will be identified during the trial, and the reporting of these safety events will be based on the clinical judgement of the site investigators. Examples of safety events may include missed injuries or missed investigations, which may be suspected if certain injuries or investigations were identified or conducted more often during the standard care phase than during the intervention phase.

All safety events will be recorded in the CRF and reported to the trial management team within 24 h of its occurrence. The trial management team will then assess if the event can be considered related to the trial or the intervention within 24 h of reporting. Events that are probably related will be reported immediately to the joint SDMC. All safety events will be followed up by the local investigator until they are fully evaluated. In addition, site investigators will report safety events based on the local ethics committee as per the Indian guidelines.

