## Trial design {8}

This is a batched stepped-wedge cluster randomised controlled trial in India (see Fig. 1). The stepped-wedge trial is a unidirectional crossover trial, with a randomised time point when clusters cross over from standard care to the intervention [33]. In this trial, the unit of randomisation is the hospital: that is, the clusters randomised to the sequences of the stepped wedge design are the hospitals. Within each hospital, one or more units of physicians performing initial resuscitation of trauma patients in the emergency department may be trained. The number of units that will be trained in each hospital will depend on the sizes of these units and the volumes of patients the physicians attend. If more than one unit is trained in the same hospital, these are all considered part of the same cluster for the purpose of randomisation.

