## Statistical methods

### Statistical methods for primary and secondary outcomes {20a}

The primary analysis set will include all observations within clusters with available data and irrespective of the receipt of the intervention. Clusters and observations within clusters will be considered exposed to the intervention after the date at which the cluster was scheduled for transition. All the data will be included except the transition phases.

We will not adjust for multiplicity of analyses because none of the secondary outcomes will be singularly more important. However, all secondary outcomes will be interpreted with due consideration for the way all are affected by the intervention without undue emphasis on a single outcome that might be statistically significant when all others appear to have remained unchanged.

We have several requirements for the analysis model. First, all analyses will consider the clustered nature of the design. Second, as the trial has only 30 clusters, it will be essential for the model to allow for correction due to the small number of clusters. Third, as the design is a stepped-wedge study, we will adjust for temporal confounding following standard approaches with categorical effects for the period of the study (1 month) [47, 48].

In the case of binary outcomes, the primary estimand will be the odds ratio obtained from a mixed effects binomial regression with a logit link. We will also apply a binomial model with an identity link to estimate the risk difference. These models will be fitted using residual pseudo-likelihood estimation based on linearisation with subject-specific expansion (RSPL). If the binomial model with the identity link does not converge then only an odds ratio will be reported.

We will include fixed effects for period and a fixed effect for intervention exposure. The primary analysis will allow for clustering as a random cluster and random cluster by period effect. To correct potential inflation of the type I error rate due to the small number of clusters, a correction for a small number of clusters will be applied. Our primary method will be a Kenward-Roger correction [49], but this choice might be updated based on new methods work available closer to the end of patient inclusion, and may differ for the outcomes collected via the complete main stepped-wedge design and incomplete nested staircase designs.

We will use a two-sided significance level of 5% and estimate 95% confidence intervals.

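### The 'only if more often in the intervention phase' rule for the three listed safety events states no adjustment for time or death, so it can misread benefit as harm or set aside a real excess

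*Protocol article*

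**What the plan says.** Section {22} of the protocol article, on adverse events and harms, explains that general adverse event collection is waived and names three events to be actively assessed in both phases: mechanical ventilation beyond 7 days, initiation of renal replacement therapy, and vasopressor use that lasts beyond 2 days or is restarted. It gives the reason for tracking them: "an increase in their occurrence following ATLS® training may indicate that the intervention is harmful". It then sets the rule for reading them: "considered indicative of harm related to the intervention only if they occur more often during the intervention phase", with standard care as the comparator.

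The same section adds two other routes. For events outside the list, "safety reports other than those mentioned above will be collected", resting on the site investigators' judgement. For every reported event, the trial management team must, within 24 hours of the report, "assess if the event can be considered related to the trial or the intervention".

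Two further places bear on the point. Trial design {8} states: "The stepped-wedge trial is a unidirectional crossover trial". Statistical methods {20a} draws the consequence for the analysis model: "we will adjust for temporal confounding following standard approaches with categorical effects for the period of the study". The three safety events are not among the outcomes in Table 1, and section {20a} does not mention them.

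**The concern.** The words 'only if' turn a comparison of phases into a gate: where no excess is seen in the intervention phase, the listed events are not to be read as harm. Two features of this trial make that comparison unreliable as the section words it.

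- **Time.** Crossover runs one way, so any secular change in case mix, intensive care capacity or recording practice falls unevenly on the two phases. Section {20a} accepts this for the outcome model; the safety rule says nothing about it.
- **Survival.** A patient who dies on day 2 cannot be ventilated for more than 7 days or receive vasopressors for more than 2. If training prevents early deaths, some of the patients saved will go on to have these events. If it causes early deaths, some of these events disappear.

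The committee could thus be alarmed by a by-product of benefit, or real harm in these events could fail the condition and be set aside. The rule also sits badly with the 24-hour relatedness assessment, because a single event cannot satisfy a condition about phase frequencies.

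**Working it through.** **Inputs from the documents.** 30 clusters in six batches of five; 13 months of inclusion per cluster, one of them transition; about 12 observations per cluster-month; mortality 20% under standard care and 15% after training (Trial design {8}, Sample size {14}).

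**The plan's own figure.** The safety rule carries none. The planned sample size reproduces: 30 × 12 analysed months × 12 = 4320.

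**Assumptions.** The figure with the sequence timings is not shown, so I took four symmetric schedules. The documents give no safety event rates or time trends; those below are illustrative.

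**1. Time gap.** With transitions in months 5, 6, 7, 8 and 9, the five clusters of a batch have 4+5+6+7+8 = 30 control months, whose month numbers sum to 10+15+21+28+36 = 110, mean 3.67. They have 30 intervention months, summing to 76+70+63+55+46 = 310, mean 10.33. The gap is 6.67 months.

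For a log-linear trend g per month, the crude ratio with no intervention effect is the mean of exp(g × month) over intervention cells divided by the same mean over control cells. It is close to exp(g × gap): exp(0.02 × 6.67) = 1.143. With a constant trend, a later batch start multiplies both means by the same factor, so batching does not remove the imbalance.

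| Assumed transition months | Gap (months) | Ratio, no effect, +2%/month | Ratio, no effect, −2%/month | Ratio, true ratio 1.15, −3%/month |
|---|---|---|---|---|
| 2, 4, 7, 10, 12 | 4.73 | 1.099 | 0.910 | 0.998 |
| 3, 5, 7, 9, 11 | 5.67 | 1.120 | 0.893 | 0.970 |
| 4, 5, 7, 9, 10 | 6.13 | 1.130 | 0.885 | 0.957 |
| 5, 6, 7, 8, 9 | 6.67 | 1.143 | 0.875 | 0.942 |

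The last column shows a real 15% excess failing the 'more often' condition under every schedule. At −2% per month the same excess would still show, barely in the tightest schedule (1.006).

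**2. Survival.** Let r be the event rate under standard care and q the share of patients saved who then have an event they would not otherwise have had. With no harm done:

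intervention rate = r + 0.05 × q

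- q = 30% to 50%: an increase of 0.05 × 0.30 = 1.5 points to 0.05 × 0.50 = 2.5 points.
- r = 10%, q = 50%: 12.5% / 10% = 1.25. With q = 25%: 11.25% / 10% = 1.13.
- r = 5%, q = 50%: 7.5% / 5% = 1.50.
- Reverse case, 5 points more early deaths, r = 10%, q = 50%: 7.5% / 10% = 0.75.

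These are upper-end values if q is read as the share of patients saved who have any such event. Some patients who die within 30 days under standard care die after day 7 and may already have counted. If p is the share of the averted deaths in which the event would have occurred anyway, the increase is 0.05 × (q − p), and it vanishes when p = q.

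**3. Adding death to the event.** With r = 10% (all in survivors) and q = 50%, event or death is 20% + 10% = 30.0% under standard care and 15% + 12.5% = 27.5% under intervention, ratio 0.92. Even at q = 100% it is 30% against 15% + 15% = 30%, so survival alone cannot make the composite rise. The converse weakness is real: a 5-point fall in deaths would cancel a true rise in non-fatal events of up to 5 points.

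**The case against.** The strongest reply is that the harms section names no estimator. 'More often' could be judged with the model in section {20a}, whose requirements are worded for all analyses, and section {17a} promises a full statistical analysis plan before the trial statistician receives data. That stands in part: that the comparison will be crude is an inference from silence, and the analysis plan may add period terms. It would not remove the survival problem or the 'only if' wording, both of which belong to the rule as stated.

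A reader might also infer that this is the trial's only systematic safety comparison and that lethal harm could go unnoticed. The documents do not support that. Table 1 has in-hospital mortality within 30 days and all-cause mortality at 24 hours, 30 days and 3 months, plus intensive care admission and lengths of stay, for all patients in both phases. Training that caused early deaths would be looked for directly there. Other safety reports, the case-level relatedness assessment and the joint steering and data monitoring committee's safety remit ({21a}) also remain. No stopping rule is tied to the phase comparison; the interim analysis ({21b}) concerns feasibility and differential recruitment.

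The 'only if' sentence has a sensible purpose: it stops events expected in this population from being blamed on training one by one. And an increase only 'may' indicate harm, so the rule does not declare harm whenever the rate rises. Finally, renal replacement counts from initiation with no minimum duration, so the survival argument is weaker for it.

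**Conclusion.** The point holds for the three listed non-fatal events. The rule makes a phase excess necessary for a reading of harm, while the phases differ systematically in time and, if training works as planned, in survival. The possible directions of error follow from the design and the event definitions; the sizes do not. They depend on assumed schedules (gap about 4.7 to 6.7 months), assumed trends (at 2% per month, crude ratios of about 1.10 to 1.14 or 0.875 to 0.910) and assumed event shares (at most about 1.5 to 2.5 points from averted deaths).

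It does not follow that harm in general would be ruled out or that the committee would have nothing else to go on. The flaw is a badly fixed interpretation rule that is cheap to repair. Should-fix, not a threat to the trial's main conclusion.

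**What to change.** Revise section {22} and carry the change into the analysis plan:

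1. Remove 'only if' as a necessary condition. Let an excess in the intervention phase trigger review by the joint committee, and say that its absence does not by itself exclude harm.
2. Compare each listed event between conditions with the period-adjusted clustered model of section {20a}, with a simpler time adjustment named in advance in case events are rare.
3. Take death into account. Report each event with death as a competing event, showing both incidences together, because the event's incidence alone will still rise when deaths are averted. Add event or death within 30 days as a supplement, not a replacement, given the masking shown above. Read all of these beside the mortality estimate and its confidence interval.
4. State how the phase-frequency rule and the 24-hour case-level relatedness assessment fit together.

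The cost is about one paragraph and a little more analysis. The events are already tracked in both phases, so no new data collection is needed. The downside is less stable models if events are few.

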## Frequency and plans for auditing trial conduct {23}

Authorised representatives for the sponsor and competent authorities (CA) may conduct audits or inspections at the trial site, including source data verification. The investigator must ensure that all source documents are available for audits and inspections. The audit or inspection will ensure that all study-related activities are performed, registered, analysed, and reported correctly and according to the protocol, ICH-GCP, and national regulations. These audits will be performed to systematically and independently review all trial-related activities and documents.

## Plans for communicating important protocol amendments to relevant parties (e.g. trial participants, ethical committees) {25}

Substantial amendments to the clinical trial protocol are possible only through approved protocol amendments and by agreement between the sponsor and the principal investigator.

## Dissemination plans {31a}

The trial will be reported to the funders within a year of completion. The results of the trial will also be prepared as manuscripts for publication. The authorship of the trial manuscripts will be based on the International Committee of Medical Journal Editors (ICMJE) criteria [53]:Substantial contributions to the conception or design of the work; or the acquisition, analysis, or interpretation of data for the work; ANDDrafting the work or reviewing it critically for important intellectual content; ANDFinal approval of the version to be published; ANDAgreement to be accountable for all aspects of the work in ensuring that questions related to the accuracy or integrity of any part of the work are appropriately investigated and resolved.

In addition to being accountable for the parts of the work completed, an author should be able to identify which coauthors are responsible for other specific parts of the work. In addition, authors should have confidence in the integrity of the contributions of their coauthors. The most recent version of the ICMJE criteria will be followed. We will also use the ICMJE criteria for nonauthor contributorship. Before work on a trial manuscript is initiated, a writing group will be formed and first and last authors will be designated. This writing group will be formed by discussion in the TMG.

## Discussion

This will be the first large-scale trial to provide robust evidence of the effectiveness of ATLS® since the programme was initiated in 1978. Regardless of the findings, this study will have important implications for trauma life support training globally. If ATLS® training improves patient outcomes, ways to promote its use and optimise its implementation, especially in low- and middle-income countries such as India, should be explored. If patient outcomes do not improve, then trauma life support training must change.

### Trial status

The current protocol version is 1.5.0, dated June 12, 2025. Inclusion of participants began on February 27, 2025. The approximate date when inclusion will be completed is November, 2029.

## Data Availability

The full protocol and statistical code will be publicly available. A deidentified anonymous dataset will also be publicly available.

## Abbreviations

ATLS: Advance Trauma Life Support
CRF: Case Record Form
ISF: Investigator Site File
TMF: Trial Master File
TMG: Trial management group
TT: Trial team
SDMC: Trial Steering and Data Monitoring Committee
